#### Control group

Participants who are recruited by a midwife centre randomly allocated to the control group will also be asked for a blood sample around 20 weeks postmenstrual age. These blood samples will be stored at -20°C, and analyzed for *C. burnetii *after delivery. In case of a positive test, the participant's general practitioner will be advised to perform an extra serological analysis to exclude chronic Q fever. Antibiotic treatment will be started if needed according to the local protocol.

### Neonates

All neonates born to Q fever positive mothers will receive care according to the local hospital protocols. The Section for Paediatric Infectious Diseases and Immunology of the Dutch Paediatric Society has formulated a consensus guideline for neonates born to Q fever positive women during pregnancy [14]. The guideline advices PCR at birth and one month of age, and serological follow up until 18 months of age in case of active maternal Q fever during pregnancy to diagnose and treat potential mother-to-child transmission. Preventive antibiotic treatment is not advised. Breastfeeding is contraindicated if maternal serum or milk is *C. burnetii *PCR positive. Breastfeeding might also be contraindicated in case of maternal medication use.

### Randomization procedure

Participating midwife centres are randomized to include either pregnant women for the control group or for the intervention group. Randomization is stratified according to the risk of contracting a *C. burnetii *infection as determined by the number of goat farms in the neighbourhood (registration by Statistics Netherlands (CBS)), and by the size of the midwife centre.

### Inclusion of participants

Pregnant women are invited by their midwife to participate in the study. The informed consent procedure will be performed by the researchers.

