## Methods/Design

Since ethical issues surrounding randomization of the individual pregnant woman for a Q fever screening or non-screening strategy could seriously threaten approval by an ethics committee, we designed a clustered randomized controlled trial in which primary care midwife centres are randomized to recruit either pregnant women for the control group or for the intervention group. In this way, the choice for either strategy by individual eligible women was avoided. Timing and phasing after eligibility checks are shown in figure 1. The study will be conducted according to the principles of the Declaration of Helsinki. The study protocol is approved by the Medical Ethical Review Board of the University Medical Centre Groningen. The study protocol is registered at http://ClinicalTrials.gov, protocol record NL30340.042.09. The inclusion of participants started in April 2010.

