### Experimental procedure

#### Intervention group

Participants who are recruited by a midwife centre randomized for the intervention group are asked for a blood sample around 20 weeks postmenstrual age. If possible the visit is combined with the routine structural ultrasound scan around that time. If the participant is included after 20 weeks, the blood sample will be taken as soon as possible after inclusion. The sample will immediately be tested for antibodies against *C. burnetii *in the laboratory of the Jeroen Bosch Hospital which has analyzed most samples during the epidemic in 2007, 2008, and 2009. Serologic diagnosis of Q fever will be made by indirect immunofluorescence assay (IFA), the reference method for serodiagnosis of Q fever [12]. Both IgM and IgG antibodies against phase I and phase II antigens are measured according to the manufacturer's instructions (Focus Diagnostics, Cypress, CA, USA). Titres ≥ 1:32 are considered positive. All positive samples will be fully titrated to reduce the chance of treatment in false positives. In general, the first antibody to appear in acute Q fever patients is IgM phase II, followed by a more or less simultaneous IgG phase II and IgM phase I response and subsequent appearance of IgG phase I antibodies (see figure 2) [13]. This time-dependent serologic profile allows us to discriminate between a recent acute infection, a past infection, and a chronic infection. If the pregnant woman does not have evidence for an acute, past or chronic Q fever infection, standard care will be provided.

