### Data collection

Data will be collected in four ways using a structured case record file:

**1. Serological samples **will be collected at the time points described in the section Experimental procedure, and will be analyzed in the laboratory of the Jeroen Bosch Hospital.

**2. Questionnaires**; two questionnaires will be filled out by the participant and one will be filled out by the midwife/obstetrician.

At baseline, when the participant is included in the trial, a questionnaire is completed by all participants including questions about the current pregnancy, outcome of previous pregnancies, smoking and alcohol habits, co morbidities, medication use and demographic characteristics. With this questionnaire risk factors are assessed for complicated pregnancy outcome. After delivery all relevant outcome data on obstetric complications are collected by a questionnaire completed by the midwife. Questionnaires for participants who are referred to a hospital during pregnancy or delivery, are filled out by the obstetrician. During follow up, all health care and potential cost data will be measured by a third questionnaire completed by the participant one month after delivery. With this questionnaire we will also verify symptoms during pregnancy, health-related quality-of-life (using EQ5D [15]), depressive symptoms and fatigue (using the Shortened Fatigue Questionnaire [16]), potential long-term consequences of Q fever, tolerance to antibiotic treatment and problems and development of the newborn. Furthermore, the risk for Q fever infection will be assessed.

**3. PCR and histo-pathology of the placenta **will be performed by the local microbiologists and pathologists. Re-evaluation of the histological slides will be performed by one pathologist at the University Medical Centre Groningen.

**4. Medical data in primary care; **data on the health status of the participant or the newborn is collected from medical files of the general practitioner.

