### Sample size calculation and statistics

Based on the literature and pilot data from The Netherlands, we expect that 12% of pregnant women in the high-risk areas will have serological evidence for a Q fever infection [17,18]. Of these women, we conservatively estimate that 25% will develop complications, so 3% of women will have the primary outcome. Assuming a reduction of the complication rate of 50% by early detection with screening during pregnancy, we will need a participation of at least 3,400 participants with complete follow up (statistical power of 80 percent, p ≤ 0.05). Assuming a loss to follow up of 10% and to allow for a small clustering effect, we aim to include 4,000 participants.

Data will be analyzed according to intention-to-screen principles. A two-sided p-value of 0.05 or less will be considered to indicate statistically significant. Descriptive statistics concerning the distributions of the predictor variables and outcome variables will be performed using the software SPSS for windows (version 16). For univariate analysis the chi-square test and Fischer's exact test will be used to compare proportions. For variables with a normal distribution, differences will be analysed with Student's t-test. In case of non-parametric distribution, differences between populations will either be evaluated using the Mann-Whitney-U test or the data will be log-transformed to obtain a normal distribution. Relative risks as well as absolute risk reductions and numbers needed to treat will be estimated with their corresponding 95% confidence intervals. Possible clustering of outcome data will be taken into account using generalised estimating equations (GEE) modelling.

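### Women are recruited after their midwife centre has been allocated, and the stated arm comparison adjusts for neither the stratification factors nor the baseline risk factors already collected

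*Protocol article*

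**What the plan says.** All references are to the protocol article.

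- **Allocation comes first.** Methods/Design states that "primary care midwife centres are randomized to recruit either pregnant women for the control group or for the intervention group", and Randomization procedure repeats it. Stratification is by goat-farm risk and centre size, both centre-level factors.
- **Recruitment follows, through the allocated centre.** Under Intervention group, the article states: "Participants who are recruited by a midwife centre randomized for the intervention group are asked for a blood sample around 20 weeks postmenstrual age". Under Control group, it states: "Participants who are recruited by a midwife centre randomly allocated to the control group will also be asked for a blood sample". Under Inclusion of participants: "Pregnant women are invited by their midwife to participate in the study". Researchers, not midwives, take consent. The text does not say whether midwives, researchers or women know the arm at that time.
- **The two offers differ visibly.** An intervention sample is tested at once and a positive result may lead to referral. A control sample is frozen and tested after delivery.
- **On choice.** Methods/Design concludes: "In this way, the choice for either strategy by individual eligible women was avoided".
- **Baseline data.** All participants complete a questionnaire covering previous pregnancy outcomes, smoking, alcohol, comorbidity, medication and demographics: "With this questionnaire risk factors are assessed for complicated pregnancy outcome".
- **Analysis.** Under Sample size calculation and statistics: "For univariate analysis the chi-square test and Fischer's exact test will be used to compare proportions". GEE is added to handle possible clustering. No covariate is named for any comparison between arms.

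**The concern.** Randomising centres balances centres, on average and within strata. It does not balance the women who agree to join when they are approached after allocation. A woman worried about exposure may be readier to join where her blood is tested now than where it is stored, and a midwife may invite differently under the two arms. If the recruited women then differ in obstetric risk or in Q fever exposure, that difference would be read as an effect of screening, or would hide one.

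The stated analysis has no step that addresses this. Allowing for clustering alters the standard error of the arm effect and leaves a difference in case mix where it was. The data for a partial remedy are already in the trial: two stratification factors known for every centre, and prognostic factors collected from every participant.

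**Working it through.** **Inputs from Sample size calculation and statistics.** Seroprevalence 12%; complications in 25% of positive women; hence 0.12 × 0.25 = 3% of all women; a 50% reduction gives 1.5%; two-sided 0.05; power 80%; 3,400 women with complete follow-up. Equal allocation is assumed, giving 1,700 per arm.

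**The plan's own figure.** For 3% versus 1.5%, with mean 2.25%:

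n = [1.960 × √(2 × 0.0225 × 0.9775) + 0.842 × √(0.03 × 0.97 + 0.015 × 0.985)]² / 0.015² ≈ 1,534 per arm (3,068 in total). With continuity correction this becomes 1,664 per arm, 3,328 in total, within 3% of the stated 3,400. The figure reproduces.

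**Expected events.** 1,700 × 0.03 = 51 in the control arm and 1,700 × 0.015 = 25.5, about 26, in the intervention arm.

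**What an imbalance would do.** The documents give none, so 10%, 20% and 30% relative differences in baseline risk are assumed. Clustering is ignored and all participants form the denominator. With d = p1 − p2, pooled standard error s0 and unpooled standard error s1,

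P(reject) = Φ[(d − 1.96 s0)/s1] + Φ[(−d − 1.96 s0)/s1].

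Example, 20% lower risk in the intervention arm and no true effect: d = 0.030 − 0.024 = 0.006 and s0 ≈ s1 ≈ 0.00556, so P ≈ Φ(−0.88) + Φ(−3.04) ≈ 0.19.

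| Assumed imbalance | No true effect: rates compared | Rejection | True RR 0.50, imbalance against screening: rates compared | Apparent RR | Power |
|---|---|---|---|---|---|
| none | 3.0% v 3.0% | 5.0% | 3.0% v 1.50% | 0.50 | 83.9% |
| 10% | 3.0% v 2.7% | 8.2% | 3.0% v 1.65% | 0.55 | 74.3% |
| 20% | 3.0% v 2.4% | 19.0% | 3.0% v 1.80% | 0.60 | 62.8% |
| 30% | 3.0% v 2.1% | 38.4% | 3.0% v 1.95% | 0.65 | 50.4% |

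**Imbalance in exposure instead.** If the recruited intervention women were 15% seropositive against 12%, the null comparison is 3.75% v 3.0%, with 22.8% rejection. With a true halving it is 1.875% v 3.0%, with 56.6% power.

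**Other denominator.** Outcome measures places the endpoint in Q fever positive women: 0.12 × 1,700 = 204 per arm. There a seroprevalence difference no longer acts directly, but a difference in underlying risk does. For 25% v 22.5%, 20% and 17.5% with no true effect, rejection is 9.1%, 22.7% and 45.7%.

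**How much a seronegative check could show.** Seronegative women number 0.88 × 1,700 = 1,496 per arm. The 95% half-width for a difference is 1.96 × √[2b(1 − b)/1,496]: 1.6 percentage points at an assumed background b of 5%, and 2.1 at 10%. A 20% relative imbalance is 1.0 point at 5% and 2.0 points at 10%, inside the interval in both cases, and clustering widens it further.

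**The case against.** The strongest reply is that only a condensed article is at hand, and a covariate list may sit in the full protocol or analysis plan. The chi-square and Fisher tests are labelled univariate, and GEE can carry covariates. This stands in part: the article does not rule out adjustment, and a missing covariate list alone would be no finding. But the article does state an analysis and gives GEE one purpose, clustering. That purpose does not answer the risk created by recruiting after allocation.

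Four stronger readings are tempting, and the document does not support them.

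- **That the arm is known at invitation and consent.** This is a reasonable inference, since each centre recruits for one arm and samples are handled differently, but it is nowhere stated.
- **That the sentence on choice is false.** It follows a remark on the ethics of randomising individual women, and a woman at a given centre does not choose between strategies. It is incomplete, because accepting or declining remains open.
- **That recruiting 4,000 of about 10,000 eligible women measures the room for selection.** The 10,000 is an estimate of eligible women living in the affected areas and the 4,000 is a target. Their ratio also depends on which centres join and is not a consent rate.
- **That bias has been shown.** Every imbalance above is assumed, and its direction can be chosen either way. The figures say what a given imbalance would do, not that this plan produces one.

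It is also fair to object that adjustment reaches only measured factors, and that the seronegative comparison is coarse and cannot reveal differing Q fever exposure. Both limits stand and belong in the plan.

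**Conclusion.** The point holds as a weakness in the stated analysis, not as a demonstrated bias. Women enter through a centre already committed to one arm, no masking is described, and the stated comparison uses neither the stratification factors nor the baseline risk factors collected from everyone. Selective participation by arm is therefore possible, and the stated analysis would leave even its measurable part uncorrected.

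The size is conditional. An assumed 10% relative imbalance does modest harm (about 8% false positives), while 20% to 30% would be serious (about 19% to 38%, or power near 63% to 50% if it ran against a true halving). This rests on 1,700 per arm, a 3% control rate, equal allocation and no clustering. The concern survives either choice of denominator.

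**What to change.** 1. Make the primary arm comparison a GEE model, clustered by midwife centre, adjusted for the two stratification factors (goat-farm risk and centre size) and a short prespecified list from the baseline questionnaire, for example previous adverse pregnancy outcome, parity, smoking and comorbidity. About 77 expected events (51 + 26) will not support a long list. State that this corrects measured imbalance only.
2. Optionally, compare obstetric outcomes by arm among seronegative women, who should be managed alike in both arms. Describe it as a check for gross imbalance only, and say that it cannot detect a difference in Q fever exposure.
3. Qualify the sentence on choice in Methods/Design: women do not choose between strategies but may accept or decline the one their centre offers. Say there who knew the centre's arm at invitation and at consent.

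**Cost:** wording and a few model terms. The covariates, the stratification factors and the seronegative women's outcomes are already collected. Sample size, recruitment, consent and clinical care do not change.

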### Data collection

Data will be collected in four ways using a structured case record file:

**1. Serological samples **will be collected at the time points described in the section Experimental procedure, and will be analyzed in the laboratory of the Jeroen Bosch Hospital.

**2. Questionnaires**; two questionnaires will be filled out by the participant and one will be filled out by the midwife/obstetrician.

At baseline, when the participant is included in the trial, a questionnaire is completed by all participants including questions about the current pregnancy, outcome of previous pregnancies, smoking and alcohol habits, co morbidities, medication use and demographic characteristics. With this questionnaire risk factors are assessed for complicated pregnancy outcome. After delivery all relevant outcome data on obstetric complications are collected by a questionnaire completed by the midwife. Questionnaires for participants who are referred to a hospital during pregnancy or delivery, are filled out by the obstetrician. During follow up, all health care and potential cost data will be measured by a third questionnaire completed by the participant one month after delivery. With this questionnaire we will also verify symptoms during pregnancy, health-related quality-of-life (using EQ5D [15]), depressive symptoms and fatigue (using the Shortened Fatigue Questionnaire [16]), potential long-term consequences of Q fever, tolerance to antibiotic treatment and problems and development of the newborn. Furthermore, the risk for Q fever infection will be assessed.

**3. PCR and histo-pathology of the placenta **will be performed by the local microbiologists and pathologists. Re-evaluation of the histological slides will be performed by one pathologist at the University Medical Centre Groningen.

**4. Medical data in primary care; **data on the health status of the participant or the newborn is collected from medical files of the general practitioner.

### Outcome measures

The primary endpoint is a maternal (chronic Q fever or reactivation) or obstetric complication (low birth weight, preterm delivery or fetal death) after the first trimester of pregnancy in Q fever positive women.

The secondary endpoints are direct and indirect costs of the screening program compared to costs of complications which could be prevented by screening. Furthermore, we aim to assess the course of infection in pregnant women, the accuracy of the diagnostic tests used for screening, histo-pathological abnormalities of the placenta of Q fever infected women, and side effects associated with treatment.

### Withdrawal of individual participants

Participants are informed that they can withdraw from the study at any time point, without giving a reason for withdrawal. If the blood sample has already been taken, participants will be asked to give permission for collecting data on obstetric outcome. Participants who withdraw will receive regular health care according to the local protocols.

### Sample size calculation and statistics

Based on the literature and pilot data from The Netherlands, we expect that 12% of pregnant women in the high-risk areas will have serological evidence for a Q fever infection [17,18]. Of these women, we conservatively estimate that 25% will develop complications, so 3% of women will have the primary outcome. Assuming a reduction of the complication rate of 50% by early detection with screening during pregnancy, we will need a participation of at least 3,400 participants with complete follow up (statistical power of 80 percent, p ≤ 0.05). Assuming a loss to follow up of 10% and to allow for a small clustering effect, we aim to include 4,000 participants.

Data will be analyzed according to intention-to-screen principles. A two-sided p-value of 0.05 or less will be considered to indicate statistically significant. Descriptive statistics concerning the distributions of the predictor variables and outcome variables will be performed using the software SPSS for windows (version 16). For univariate analysis the chi-square test and Fischer's exact test will be used to compare proportions. For variables with a normal distribution, differences will be analysed with Student's t-test. In case of non-parametric distribution, differences between populations will either be evaluated using the Mann-Whitney-U test or the data will be log-transformed to obtain a normal distribution. Relative risks as well as absolute risk reductions and numbers needed to treat will be estimated with their corresponding 95% confidence intervals. Possible clustering of outcome data will be taken into account using generalised estimating equations (GEE) modelling.

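### The primary endpoint is defined in Q fever positive women but sized over all recruited women; the denominator should be fixed, and seropositive women are the more efficient choice

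*Protocol article*

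**What the plan says.** Under Outcome measures, the primary endpoint is a maternal or "obstetric complication (low birth weight, preterm delivery or fetal death) after the first trimester of pregnancy in Q fever positive women". The Abstract likewise places the endpoint in Q fever positive women.

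Under Sample size calculation and statistics, the chain is: "we expect that 12% of pregnant women in the high-risk areas will have serological evidence for a Q fever infection"; of these, "we conservatively estimate that 25% will develop complications"; "so 3% of women will have the primary outcome". The effect is stated as "Assuming a reduction of the complication rate of 50% by early detection with screening during pregnancy", with "statistical power of 80 percent, p ≤ 0.05", giving at least 3,400 women with complete follow-up and a recruitment target of 4,000. The analysis is by intention to screen, and "Relative risks as well as absolute risk reductions and numbers needed to treat will be estimated", with no denominator named. Clustering is to be handled with GEE.

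Two other parts of the design matter. Both arms give a blood sample at about 20 weeks, tested at once in the intervention arm and after frozen storage and delivery in the control arm (Experimental procedure). Centres are randomised within strata of goat-farm numbers and centre size (Randomization procedure).

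**The concern.** The endpoint definition points to one population and the sample size to another. This goes beyond detail that an analysis plan could supply, because the article itself uses both. The two readings give different tests, different absolute effects and different numbers needed, and the choice could be made after the results are known.

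The choice also affects precision. With all women as the denominator, an event requires both seropositivity and a complication. Screening cannot change serostatus on the 20-week sample, so differences in seroprevalence between centres only add noise to the comparison. Such differences are to be expected when recruitment areas are chosen by local incidence and randomisation is stratified on a proxy for infection risk. Serostatus is available in both arms from the same time point, so the noise can be avoided with data already being collected.

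**Working it through.** **Inputs from the article:** seroprevalence 12%, complication risk 25% in positives, relative reduction 50%, two-sided 0.05, power 80%, N = 3,400. **Assumed:** 1:1 allocation, number of centres, between-centre coefficient of variation (CV) of seroprevalence.

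**1. Reproducing 3,400.** For two proportions, n per arm = [1.96√(2p̄(1−p̄)) + 0.842√(p₁(1−p₁)+p₂(1−p₂))]²/(p₁−p₂)².
- All women, 3% v 1.5%: (0.4111 + 0.1763)²/0.015² gives 1,534 per arm, 3,068 in total. With continuity correction, 1,664 per arm and 3,328 in total, 2.1% below 3,400. The stated figure is therefore the all-women calculation, rounded up.

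**2. The same formula among positives, 25% v 12.5%.** (1.0819 + 0.4586)²/0.125² gives 152 per arm, 304 positives, or 304/0.12 = about 2,533 women. With continuity correction, 168 per arm, 336 positives, or 336/0.12 = 2,800 women.

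**3. Power at 3,400 without clustering** (no continuity correction).
- All women, 1,700 per arm: (0.015 − 1.96 × 0.005087)/0.005080 = 0.99, power 84%.
- Positives, 3,400 × 0.12 = 408, 204 per arm: (0.125 − 1.96 × 0.03865)/0.03815 = 1.29, power 90%.
- With continuity correction the pair is 81% and 88%.

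**4. Absolute effects.** All women: 1/(0.03 − 0.015) = 67. Positives: 1/(0.25 − 0.125) = 8.

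**5. Power over all women when seroprevalence varies by centre.** If seroprevalence has SD 0.12 × CV, the outcome ICC is ρ₁ = (0.25 × 0.12 × CV)²/(0.03 × 0.97) in controls and ρ₂ = (0.125 × 0.12 × CV)²/(0.015 × 0.985) under the design effect. With m women per centre, D = 1 + (m − 1)ρ, SE² = (0.0291 D₁ + 0.014775 D₂)/1,700, and power = Φ(0.015/SE − 1.96).

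Example, 50 centres (m = 68), CV 0.5: ρ₁ = 0.00773, ρ₂ = 0.00381, D₁ = 1.518, D₂ = 1.255, SE = 0.00607, power = Φ(0.51) = 69.5%.

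| Centres | CV 0.2 | CV 0.3 | CV 0.5 |
|---|---|---|---|
| 30 | 79.8% | 74.9% | 61.5% |
| 50 | 81.5% | 78.5% | 69.5% |
| 80 | 82.4% | 80.5% | 74.7% |

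Simulation with a cluster-level test at CV 0.5 gave 60%, 70% and 75% for 30, 50 and 80 centres, with type I error near 5%. A cluster-robust test among positives kept 87% to 90% power, with complication risk assumed not to cluster.

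**6. Imbalance in a single trial.** With 25 centres per arm and CV 0.5, centre variation alone gives the arm difference in seroprevalence an SD of √(2 × 0.06²/25) = 0.017, before any gain from stratification. A 13% v 11% split with no screening effect gives 3.25% v 2.75%, an apparent relative risk of 0.85. Among positives it stays 25% v 25%.

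**The case against.** A reader might infer that uneven seroprevalence would pass as a screening effect and inflate the false-positive rate. A chi-square test that ignores clustering and stratification does behave that way: at CV 0.5 and 30, 50 and 80 centres, simulated type I error was 15.8%, 13.0% and 9.0%. The documents do not support that reading, because the article plans GEE for clustering and stratifies on goat farms. Once clustering is respected, chance differences between centres are carried in the standard error, and a cluster-level test held about 5%. That test stood in for GEE, which was not itself simulated.

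It can also be said that the all-women denominator is legitimate. The trial evaluates a screening policy, the analysis is by intention to screen, and a seropositive complication per woman offered screening suits the economic aim. On that view, "after the first trimester of pregnancy in Q fever positive women" is part of the event definition, and the 8 and 67 are two different quantities. This stands as a defence of coherence. It does not settle which denominator the reported estimates will use, and it does not recover the lost precision.

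Restricting to positives does not in itself break the randomised comparison, since the sample is taken before any result-driven care and women stay in the arm of their centre. The point that does stand is that immediate and frozen-sample testing must give comparable positivity. That condition also affects the all-women event, which requires a positive test.

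**Conclusion.** The concern holds as an unfixed and inefficient denominator. It is not an arithmetic error, since 3,400 is sound for all women without clustering, and it is not a systematic bias.

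The firm part of the loss is about 6 points of power at 3,400 (84% v 90%), or 2,800 v 3,328 women for 80% power with continuity correction. The larger part, about 60% to 82% v about 90%, depends on assumed centre numbers and CV, and on complication risk not clustering among positives. At CV 0.2 the all-women analysis stays close to its 80% target; 60% is the high-variation, few-centre end. Recruiting the full 4,000 leaves 3,600 after 10% loss, which helps only slightly: with 50 centres and CV 0.5, m = 72 gives SE = 0.00596 and power Φ(0.56) = 71%.

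Stratification should reduce imbalance, but goat-farm count is a proxy. GEE widens the interval for clustering without removing a chance seroprevalence difference from the one trial's estimate.

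**What to change.** - Make the primary comparison the complication risk among women seropositive on the index (about 20-week) sample, analysed in the arm of their centre, with GEE for clustering and these women as denominator for the relative risk, absolute risk reduction and number needed to treat.
- Restate the sample size on 25% v 12.5% of positives, with the implied number recruited at 12% seroprevalence.
- Report the all-women risk difference as secondary, labelled number needed to screen.
- Report seroprevalence by arm, to check that immediate and frozen-sample testing give comparable positivity.

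The cost is wording in the protocol and analysis plan; no new data are needed. The small downside is that the headline result becomes conditional on seropositivity and relies on that comparability.

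### After 10% loss, 4,000 women leave a design effect of only 1.06 (at most about 1.17) for randomising centres, so the unqualified 80% power holds only if clustering is small

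*Protocol article*

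**What the plan says.** All the sizing figures are in the protocol article under Sample size calculation and statistics. Twelve percent of women are expected to be seropositive. The article continues: "Of these women, we conservatively estimate that 25% will develop complications, so 3% of women will have the primary outcome". The effect is specified as follows: "Assuming a reduction of the complication rate of 50% by early detection with screening during pregnancy". The test is two-sided at 0.05, and the requirement before any inflation is 3,400 women with complete follow-up for 80% power. The recruitment target follows in one step: "Assuming a loss to follow up of 10% and to allow for a small clustering effect, we aim to include 4,000 participants".

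Under Randomization procedure, the unit is the centre: "Participating midwife centres are randomized to include either pregnant women for the control group or for the intervention group". Randomisation is stratified by centre size and by the local risk of infection, "as determined by the number of goat farms in the neighbourhood". The analysis plan is to handle clustering with generalised estimating equations (GEE). The article gives no ICC, design effect, number of centres or centre size.

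**The concern.** The 600 women added to 3,400 must cover two things, loss and clustering, and loss takes most of them. What remains is a thin margin for a trial in which whole centres are allocated.

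The plan also gives a reason to expect centres to differ. It stratifies on goat-farm exposure because infection risk depends on location. The sized outcome is the product of seroprevalence and complication risk among all women, so differences in seroprevalence between centres feed directly into it.

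If the margin is too small, the true power is below the stated 80%. A null result could then be read as evidence against screening, which is the policy question the trial is meant to inform.

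**Working it through.** **Inputs from the article.** Control rate p1 = 0.12 × 0.25 = 0.03; intervention rate p2 = 0.015; difference Δ = 0.015; two-sided alpha 0.05; power 80%; 3,400 completers; 10% loss; 4,000 enrolled. **Assumed, because the article does not give them:** 1:1 allocation, m = 20, 40 or 60 women per centre, and the between-centre CV.

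**1. Reproduce 3,400.** The standard formula for two individually randomised proportions gives 1,534 per arm, 3,068 in total. With continuity correction it gives 1,664 per arm, 3,328 in total, which is within 3% of 3,400. The 3,400 therefore appears to contain no clustering allowance.

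**2. Room left for clustering.**
- Loss alone: 3,400/0.9 = 3,778, which uses 378 of the 600 added women. The other 222 are left for clustering.
- Completers: 4,000 × 0.9 = 3,600.
- Design effect covered on the plan's requirement: 3,600/3,400 = 1.059.
- On the uncorrected requirement: 3,600/3,068 = 1.173. Without clustering, 3,600 completers give 85.9% power by the uncorrected formula.

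**3. Largest ICC covered.** With design effect DE = 1 + (m − 1) × ICC, the largest ICC is (DE − 1)/(m − 1).

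| Women per centre | DE 1.059 | DE 1.173 |
|---|---|---|
| 20 | 0.0031 | 0.0091 |
| 40 | 0.0015 | 0.0045 |
| 60 | 0.0010 | 0.0029 |

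**4. Power at 4,000 for an assumed CV of centre rates, the same in both arms.**
- The arm-specific ICC is (CV × p)²/[p(1 − p)]. At CV 0.5 it is 0.0077 for p = 0.03 and 0.0038 for p = 0.015.
- The two arms' design effects are weighted by p(1 − p), which is 0.0291 and 0.014775. At m = 40: (0.0291 × 1.302 + 0.014775 × 1.148)/0.043875 = 1.25.
- Effective n per arm is 1,800/DE; at m = 40 it is 1,440.
- Power = Φ{[Δ√n − 1.96√(2 × 0.0225 × 0.9775)]/√0.043875}. At n = 1,440 this is Φ(0.755) = 0.775.
- For the continuity-corrected value, n is replaced by (n − 1/Δ)²/n. At m = 40 this is (1,440 − 66.7)²/1,440 = 1,310, giving Φ(0.629) = 0.735.

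| CV | Women per centre | Design effect | Power, uncorrected | Power, corrected |
|---|---|---|---|---|
| 0.5 | 20 | 1.12 | 82% | 78% |
| 0.5 | 40 | 1.25 | 78% | 74% |
| 0.5 | 60 | 1.38 | 73% | 69% |
| 0.3 | 20 | 1.04 | 84% | 81% |
| 0.3 | 40 | 1.09 | 83% | 80% |
| 0.3 | 60 | 1.14 | 81% | 78% |

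These figures take equal centre sizes and no adjustment for strata.

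**The case against.** The plan does acknowledge clustering, both in the target and in the analysis. A condensed article may also leave the ICC and the number of centres to the full protocol. Both points stand: clustering has not been ignored, and the missing inputs are not in themselves the defect. What can be tested is the margin, because the article fixes all three figures that determine it.

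A reader might infer that 80% power survives only at an ICC of practically zero. The documents do not support that. A GEE analysis carries no continuity correction, and without one the room is about 1.17. For a 3% outcome even a CV of 0.3 corresponds to an ICC of only (0.3 × 0.03)²/(0.03 × 0.97) = 0.0028, and power then stays near 80%. At a CV of 0.5 with 20 women per centre it is still 82% uncorrected. Nor do the documents show which CV or centre size is realistic. Applying the control-arm ICC of 0.0077 to both arms would give a gloomier 76% and 71% at 40 and 60 per centre (uncorrected), but a constant CV implies about half that ICC in the intervention arm.

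Stratification also works in the plan's favour. It tends to balance exposure between arms and could recover some power if the strata enter the model. The article does not say that they do, so no gain can be counted. GEE by itself makes the standard errors honest but does not restore lost power, and unequal centre sizes would reduce it further.

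Finally, the Outcome measures section defines the endpoint in Q fever positive women. In that comparison only about 0.12 × 40 = 5 women from a centre of 40 would contribute, and clustering of seroprevalence largely drops out. The figures here apply to the all-women comparison on which the trial was sized.

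**Conclusion.** The point holds as a limit on the stated power. The article's own numbers leave a design effect of 1.06 for centre randomisation, or about 1.17 under the more lenient reading of 3,400. The 80% for 3% versus 1.5% among all women is then conditional on small clustering, a condition that the article does not quantify.

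The shortfall depends on assumptions. At a CV of 0.3 there is little or none. At a CV of 0.5 it runs from none (20 per centre, uncorrected) to about 11 percentage points (60 per centre, corrected). The documents establish the thin margin; they do not establish that the trial is underpowered.

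**What to change.** In Sample size calculation and statistics, replace the unqualified 80% with two statements: the design effect that 4,000 covers (1.06 on the plan's basis), and the power at 4,000 over a stated ICC range. Use the actual number and sizes of the participating centres, and say whether a continuity correction applies. Include the randomisation strata (goat-farm exposure and centre size) in the GEE model. If the primary comparison is in Q fever positive women only, recompute the power for that population.

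No extra recruitment is needed. The cost is a restated power that is likely to be less favourable than 80% over part of the range.
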